### Feasibility of the outcomes measuring for the future definitive trial

In the pilot trial, we are testing the *primary endpoint* for the future definitive trial, which will be the combined endpoint of health-related patient outcomes (hospitalization, falls, and mortality), as shown in Table 1. *Secondary endpoints* for the future definitive trial will include improvement in information on medications (SIMS-D questionnaire [44]), a reduction in symptoms and/or side effects of the medication (pro-CTCAE questionnaire [45, 46] adjusted), an improvement in health literacy (HLQ-G questionnaire [47]), and improving the medication and treatment-related information: comparing the available information regarding the care situation between GP and patient (FIMA [48, 49]).

**Table 1 Tab1:** Description of the combined endpoint for the future definitive trial

**Endpoint (quantity)**	**Patients**		**GP Practice**	
	**Data**	**Instrument**	**Data**	**Instrument**
Hospitalization	X	Single question regarding hospitalization including frequency and length of stay from FIMA [48, 49]	X	Single question regarding hospitalization including frequency and length of stay from FIMA [48, 49]
Falls	X	Standardized documentation (self-report)		
Mortality			X	Standardized documentation

### Data collection methods for the planned outcome measures for the future definitive trial

In addition to the process evaluation, an overview of what data will be collected and when is shown in Fig. 2. Data are collected for both the IG and the CG.

**Fig. 2 Fig2:**
[figure not shown]
Assessments conducted as part of HYPERION-TransCare

#### GP practice

At *baseline*, information on the practice (such as practice size, practice type, and location), as well as sociodemographic information for the GPs and HCAs (such as sex, age, professional experience), will be collected using a self-administered questionnaire. Furthermore, the diseases of each included patient will be collected by 14 disease groups (based on the “Cumulative Illness Rating Scale” (CIRS) [50]).

At both *baseline* and *follow-up*, the standardized and validated FIMA questionnaire [48, 49] will be collected for each included patient. The FIMA (German acronym for “Questionnaire for Health-Related Resource Use in an Elderly Population” — Fragebogen zur Erhebung von Gesundheitsleistungen im Alter) “collects the health-related resource use within the older population groups” [48]. The questionnaire will be slightly modified, so that the questions are suitable for use in GP practices and reflect the patient data that is available to them. As an alternative to entering medications in the FIMA, practices may also send a copy of an existing medication plan to the study team. Mortality will be surveyed during the study (standardized documentation).

#### Patients

At *baseline*, a self-administered questionnaire will be used to collect data on sociodemographic characteristics (such as sex, age, and living situation), as well as knowledge and use of an electronic patient file (ePA in Germany). At both *baseline* (t0) and *follow-up* (t1), a medication plan will be required, along with information on the number of falls within the last 3 months (based on the WHO definition [51]) and on symptoms and/or side effects of the medication (selection of the German patient-reported outcomes version of the Common Terminology Criteria for Adverse Events (NCI PRO-CTCAE™ Items-GERMAN [45, 46]). Furthermore, validated and standardized questionnaires will be used:FIMA: Fragebogen zur Inanspruchnahme medizinischer und nicht-medizinischer Versorgungsleistungen im Alter (Questionnaire for Health-Related Resource Use in an Elderly Population) [48, 49]HLQ-G: Health Literacy Questionnaire — German [47]SIMS-D: Satisfaction with Information about Medicines Scale, German version [44]

Patient enrolment is scheduled to start in March and will be completed in May 2022. Data collection is expected to end in November 2022. The participant timeline is shown in Table 2.

**Table 2 Tab2:**
[figure not shown]
Participant timeline (SPIRIT 2013 diagram [32])

^*^For exact list of assessments, see Fig. 2

### Sample size

Since this is a pilot study, we did not perform a sample size calculation [29]. A number of 10 practices per site (Saxony and Hesse) as well as 10 patients per practice seemed to be a practical value that would be sufficiently informative regarding the feasibility of the study, even with some dropouts.

### Data management

Surveys conducted in the GP practices will take place digitally using an Electronic Data Capture-System (REDCap; hosted via the Coordination Center for Clinical Studies of the TU Dresden (KKS); storage on German servers). Patients will receive paper-based questionnaires (baseline questionnaire issued by GP practices; follow-up questionnaire sent by the study team), which will be returned directly to the study team in stamped addressed envelopes. The study team will then enter the data into REDCap. Semi-structured interviews with patients and GP practices will be conducted by telephone, recorded, and then transcribed verbatim.

A data protection concept was developed to take into account the legal directives (EU General Data Protection Regulation, national data protection law (Federal Data Protection Act) as well as regional directives, i.e., the Hessian and Saxonian data protection laws). In addition, an agreement on the joint processing of personal data was concluded between the study teams. The data will be treated confidentially at all times, and pseudonymized data will not be provided or made available to third parties.

According to the FAIR principles [52], anonymized data sets can be provided to others for future research. The data will only be passed on if certain rules are observed (e.g., approval by an independent ethics committee, use in medical research, application for use). The management of the two study teams will carefully review applications and decide, according to standardized criteria, whether to provide the data to the interested research group for the described research purpose.

Study consent can be withdrawn by practices or patients at any time without giving reasons to the study team and at no disadvantage to themselves. In this case, no further data will be collected, and existing data will be deleted. However, consent withdrawal will not affect data that has already been analyzed. After termination or discontinuation of the study, the data will be archived for up to 10 years in the protected databases of the two study teams. The databases will be secured against unauthorized access.

Participants are monitored regularly (e.g., telephone calls, checked REDCap entries). Irregularities noticed in the course of the study will be systematically documented or recorded as part of the process evaluation. Nonparticipants (date, sex, year of birth, reasons) as well as withdrawals and study discontinuations (date and reason, if known) will be documented. A dropout is defined as a patient that changes GP practices during the study phase, is admitted to a nursing home, or is no longer interested in participating in the study. Follow-up recruitment to compensate for dropouts will not take place because of the pilot study design. The analysis of the participation processes should provide important information to help in the design of the subsequent future definitive trial.

A plausibility check will be performed via REDCap. Data checks will ensure the data is of high quality. Data cleaning will be carried out independently of the study team by the cooperation partner of Ruhr University Bochum.

### Analysis

Wherever appropriate, interview transcripts will undergo content analysis based on Mayring [53] and through the use of MAXQDA. Quantitative and qualitative data will be analyzed descriptively with focus on the following:
*Feasibility*
The recruitment and randomization process will be presented descriptively. Adherence to the planned way of realization will be assessed. Furthermore, a descriptive analysis will be performed to compare the two study groups.Content-oriented description of participants’ comprehension of and adherence to the intended implementation of the intervention’s components, their expectations, and experiences throughout the study periodAnalysis for the maintenance of blinding will be done at patient and cluster level. At a patient level, mixed logistic regression analysis will be performed with dependent variable “patient correctly guess treatment group” and independent variable treatment group and a random cluster effect. Similar, at cluster level, logistic regression analysis will be performed with outcome “GP correctly guess treatment group” and independent variable treatment group. If the random cluster effect in the analysis at patient level is large, we will further explore the association between GPs guess and patients guess through logistic regression.
*Exploration of possible effects*: One possible effect of the intervention is an improvement in health literacy, as assessed using the HLQ-G. A linear mixed model that employs intervention group, HLQ-G at baseline, age, sex, and cluster as the independent variables will be used to evaluate the effects.
*Analysis of the combined endpoint*: A mixed logistic regression model will be used to analyze the planned combined endpoint, which is a combination of death, hospitalization, and falls (dichotomous), similar to the analysis planned in the main trial. In addition to study group, age and sex will be included as fixed effects, with the cluster added as a random effect. If a significant proportion of patients (> 10%) experience multiple events for falls and hospitalizations, we will perform additional separate analyses for these outcomes that uses a mixed negative binomial model. The sample size calculation for the future definitive trial will be based on the results of these models. Sensitivity analyses will be performed for per-protocol group.Agreement and differences in FIMA results between patients and GPs will be analyzed using agreement parameters such as Kappa statistics.

The resulting assessment of the clinical relevance of the outcomes and the findings of the process evaluation will be used in planning the future definitive trial. Statistical analyses of intervention effects will be performed as part of the future definitive trial. Exploratory analyses will be performed according to the intention to treat principle.

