## Methods/design

An exploratory, prospective, cluster-randomized pilot study (including process evaluation) will be conducted. The multicenter two-arm study (parallel groups) will be conducted in 20 GP practices in Hesse and Saxony (Germany), whereby each practice will be asked to recruit 10 patients, bringing the total to 200 patients.

We will compare the results of the complex intervention for improving information availability in preparation for the transition of care in an intervention group (IG), with the results of a control group (CG) that will receive usual care, i.e., in accordance with German GP practice guidelines [30, 31].

The study complies with the Declaration of Helsinki and was approved by the Ethics Committee of the Technical University of Dresden, the Ethics Committee of the Department of Medicine of Goethe University Frankfurt am Main, and the Ethics Committee of the Medical Faculty of the University of Heidelberg. The study protocol follows the SPIRIT 2013 guidelines [32], adapted according to Thabane und Lancaster (2019) [33] (see Additional file 1) and the CONSORT 2010 statement [34] (see Additional file 2) and was registered in the German Clinical Trials Register (DRKS).

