### Allocation and blinding

To avoid contamination of the IG and CG, the level of randomization will be the GP practice (cluster randomization) stratified based on study site. Upon inclusion, each GP practice will be allocated a consecutive number by the study team (pseudonym). In preparation for block randomization, an online tool [38] will be used to generate a random list of the two study arms in blocks of 6 and 4 for each study region. The pseudonym of the practices will be entered into the randomization list in the order in which participating patients from a specific GP practice complete the baseline surveys (t0). The GP practice will thus be randomly assigned to one of the study arms. The randomization process will be administered confidentially by two researchers from one of the study teams’ institutes that are not involved in the study.

All participants will be blinded. After block randomization, GP practices will receive study materials and training according to their assigned study arm (training part 2, digital). After completion and evaluation of the study, all participants will receive a booklet containing an overview of the methodology and main results of the study. The statistical analysis will be performed by blinded staff at Ruhr University Bochum (cooperation partner).

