#### Control group

During the 6-month intervention phase, treatment for participants (GP practices and patients) randomly assigned to the CG will be “care as usual.” This means that treatment will be provided in accordance with established evidence-based medical guidelines. As in the intervention group, medical guidelines for the management of multimorbidity and polypharmacy (for GP practices), as well as the patient flyer (for patients), will be provided to the control group. This procedure will serve to blind the participants.

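### The blinding models regress correct guessing on arm, so the arm coefficient measures asymmetry between the arms rather than whether guesses track allocation

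*Protocol article*

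**What the plan says.** The Allocation and blinding section states that "All participants will be blinded". The Control group section explains that controls also receive the guidelines and the patient flyer, and adds: "This procedure will serve to blind the participants". Only the intervention group receives the patient portfolio and the practice checklist.

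Under Feasibility, the Analysis section says how the maintenance of blinding will be examined. For patients it is a mixed logistic regression with "dependent variable “patient correctly guess treatment group” and independent variable treatment group and a random cluster effect". For practices, "logistic regression analysis will be performed with outcome “GP correctly guess treatment group” and independent variable treatment group". There is one conditional further step: "If the random cluster effect in the analysis at patient level is large, we will further explore the association between GPs guess and patients guess".

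The section does not say which parameter of these models will be read as evidence on blinding. It plans no comparison of correct guessing with chance, no regression of the guess itself on arm, and no blinding index. It sets no threshold.

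**The concern.** Blinding has held if a participant's guess is unrelated to the arm that the participant is in. Once the outcome is recoded from the guess to whether the guess was right, the arm term no longer addresses that question. It asks whether one arm guesses right more often than the other. The two questions can have opposite answers.

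Both troublesome patterns are plausible here. The portfolio and checklist could reveal the allocation. Conversely, if the flyer and guidelines work as intended, many controls may believe that they are in the intervention group, so that guesses lean the same way in both arms.

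The pilot is meant to test the feasibility of the study design, and its results will be used to plan the definitive trial. Falls are reported by patients alone, and the medication-information, symptom and health-literacy questionnaires are completed by patients. A wrong reading of the blinding result could carry an ineffective blinding scheme forward, or discard one that works.

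**Working it through.** **Inputs.** From the Methods/design section: 20 practices, and "each practice will be asked to recruit 10 patients, bringing the total to 200 patients". From Allocation and blinding: an online tool will "generate a random list of the two study arms in blocks of 6 and 4 for each study region". The ratio is not stated, so I assume 1:1, with 10 practices and about 100 patients per arm. The article gives no expected guess rates, so all rates below are assumptions. It reports no figure for the blinding analysis, so there is none to reproduce.

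**Algebra.** Let p1 and p0 be the probabilities of guessing 'intervention' in the intervention and control arms. The proportions correct are p1 and 1 − p0.

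- Planned arm coefficient: logit(p1) − logit(1 − p0) = logit(p1) + logit(p0).
- Association of guess with allocation: logit(p1) − logit(p0).

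If blinding fails equally, p1 = 1 − p0 and the planned coefficient is 0. If guesses are uninformative, p1 = p0 = p and it is 2·logit(p), which is 0 only at p = 0.5.

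| Assumed pattern | p1 | p0 | Correct, intervention / control | Planned OR | OR of guess on arm |
|---|---|---|---|---|---|
| Blinding lost equally | 0.85 | 0.15 | 85% / 85% | 1.00 | 32 |
| Blinding lost equally | 0.90 | 0.10 | 90% / 90% | 1.00 | 81 |
| Uninformative, 50/50 | 0.50 | 0.50 | 50% / 50% | 1.00 | 1.00 |
| Uninformative, 60% lean | 0.60 | 0.60 | 60% / 40% | 2.25 | 1.00 |
| Uninformative, 70% lean | 0.70 | 0.70 | 70% / 30% | 5.44 | 1.00 |
| Unblinded in intervention arm only | 0.90 | 0.50 | 90% / 50% | 9.00 | 9.00 |

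Examples: (0.85/0.15)² = 32; (0.70/0.30)² = 5.44; (0.60/0.40)² = 2.25. The last row shows that failure in one arm does move the planned coefficient. It cannot be told apart from a shared lean, however: an uninformative 75% lean also gives (0.75/0.25)² = 9.

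**Precision, ignoring clustering, 100 per arm.** At a 70% lean, SE = √(2/(100 × 0.70 × 0.30)) = 0.309 and z = ln(5.44)/0.309 = 5.5. At a 60% lean, SE = √(2/(100 × 0.60 × 0.40)) = 0.289 and z = ln(2.25)/0.289 = 2.8, p = 0.005.

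**With clustering.** In a simulation of 20 practices of 10 patients (random-intercept SD 0.5 on the logit scale, 500 replicates, an exchangeable logistic GEE standing in for the mixed model, two-sided 5% for illustration), the planned arm term was significant in:

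- 6.0% of replicates when 90% guessed correctly in both arms;
- 7.2% with 50/50 guessing, 59.8% with a 60% lean and 99.2% with a 70% lean.

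Regressing the guess on arm gave 100% in the first case, and 7.2%, 7.4% and 8.2% in the three uninformative cases. The last three figures lie a little above 5%, with only 20 clusters in the GEE.

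**What the planned model does contain.** With intercept a = logit(1 − p0) = −logit(p0) and arm term b = logit(p1) + logit(p0), the sum 2a + b = logit(p1) − logit(p0). This is exactly the contrast needed.

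**GP level.** With 10 practices per arm, one guess per practice and the same rate q of correct guessing in both arms, the chance that every GP in at least one arm is right is 1 − (1 − q¹⁰)². That is 0.355 at q = 0.85 and 0.58 at q = 0.90. When it happens, the logistic estimate is infinite. At q = 0.70 the chance is only about 6%.

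**The case against.** The strongest defence is that the planned model loses no information. Arm is its only fixed effect, so it yields the correct-guess rate in each arm, and 2a + b recovers the association of guess with allocation. The article never says that the arm coefficient alone will be the verdict, and it describes the quantitative analysis as descriptive. All of this stands. The defect therefore lies in what the plan says it will estimate, and not in a model that is incapable of answering. But arm is the only predictor named, no other contrast is planned and no comparison with chance is mentioned, so the natural reading of the output is the misleading one.

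A reader might infer more than the document supports on four points:

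- **That any uninformative guessing gives a strong effect.** It does not. At 50/50 the odds ratio is 1, and a lean towards one arm is needed.
- **That the follow-on rule on a large cluster effect is also compromised.** It is not. All patients in a practice share one arm, so recoding only flips the sign of a symmetric random intercept in control practices. The cluster variance, and so the trigger, is the same under either coding.
- **That separation at GP level is to be expected.** It becomes more likely than not only at about 90% correct, when a simple count would already show that blinding had failed. Recoding the outcome does not remove it.
- **That every outcome is exposed to unblinded self-report.** Table 1 has mortality documented by the practice and hospitalization reported by both practice and patient.

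**Conclusion.** The point holds in this limited form. The arm coefficient in both planned models measures asymmetry in correct guessing. It is null when blinding fails equally in both arms, and non-null when uninformative guesses lean to one side (odds ratio 2.25 at a 60% lean, 5.4 at 70%). The first result is exact for any common rate of correct guessing. The sizes in the second rest on assumed guess rates, and the significance figures rest on assumed 1:1 allocation and, in the simulation, an assumed cluster variance.

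This is not something left to the statistical analysis plan, because the article already fixes the outcome and the predictor. The consequence is confined to the feasibility conclusion on blinding that informs the definitive trial. No effect estimate is touched, and the article ties no decision threshold to the blinding models. It should be fixed, but it is not critical to the pilot.

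**What to change.** At patient level, make 'guessed intervention group' the dependent variable and keep arm as predictor and practice as random effect, so that an odds ratio of 1 means that guesses are unrelated to allocation. Keeping the planned model and reporting 2a + b with its confidence interval would be equivalent.

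Alongside it, report the proportion correct in each arm against 50% with cluster-adjusted confidence intervals. The two proportions should be read together: both above 50% points to lost blinding, while one above and one below by the same amount points to a shared lean.

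At GP level, give the 2x2 table of guess by allocation with an exact test, which avoids infinite estimates if an arm is entirely correct. With about 20 practices, a non-significant result should not be taken as proof that blinding held. The follow-on step on GP and patient guesses can stay as it is.

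The cost is a sentence or two in the Analysis section. No additional data are needed.

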### GP practices

For the implementation of the complex intervention, GP practices in the intervention group will receive a “GP practice Checklist,” which will be used separately for each study patient. The checklist can be completed and saved on paper or digitally, depending on preference. The checklist helps the GP practice administer and complete the *patient portfolio* as well as to complete the information in the GP practice´s documentation. It contains a list of information (e.g., disease-specific data, information on medication, personal data, documents, special features, and notes) that is important for both the GP practice and patients as well as in case of hospitalization. The date on which the checklist and notes were last updated will also be entered. The checklist includes an indication whether the information is more likely to be provided by the GP practice or the patient.

In a pretest, the checklist was evaluated in a telephone interview with two GPs and two HCAs with regard to completeness, manageability, and layout and was then adapted and finalized. The intervention aims to support the patients’ self-management skills and knowledge about their health status. It should furthermore contribute to a more complete set of information on the side of the patient and in turn more comprehensive information for healthcare providers.

In addition, the GP practice will receive information from the abridged version of the German GP guidelines on polypharmacy and multimorbidity [30, 31].

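### The GP-level blinding model, a logistic regression on about 10 GPs per arm, has no finite odds ratio if every GP in one arm guesses correctly; exact proportions per arm should carry the result

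*Protocol article*

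**What the plan says.** The Analysis section of the protocol article (Feasibility item on blinding) plans two models. Patients' guesses are analysed by mixed logistic regression with a random cluster effect. For the GPs, "at cluster level, logistic regression analysis will be performed with outcome" "GP correctly guess treatment group" and treatment group as the independent variable. No penalised or exact variant is named, and neither is a test statistic, significance level or decision rule. The section is introduced by the statement that "Quantitative and qualitative data will be analyzed descriptively with focus on the following".

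Methods/design and Sample size give 20 practices, 10 in each of two regions. Allocation and blinding describes a "random list of the two study arms in blocks of 6 and 4 for each study region". The Sample size section adds: "Since this is a pilot study, we did not perform a sample size calculation".

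Intervention practices receive a checklist "which will be used separately for each study patient" (section GP practices), and their patients receive a portfolio. Control practices have neither, but under Control group they receive the same guideline material, and their patients the same flyer, in order to support blinding.

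**The concern.** A logistic regression with one binary predictor and about 10 binary outcomes per arm is a model of a 2x2 table. If all GPs in one arm answer correctly, that arm has no wrong guesses and one cell is empty. The likelihood then keeps rising as the coefficient grows, so there is no finite estimate. Software stops at an arbitrary large value with an enormous standard error.

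Intervention GPs handle a patient-level checklist and help with portfolios, so they have a cue to their arm. Complete correct guessing in that arm is a plausible outcome, and it is the one that a blinding check most needs to show.

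What is at stake is the usefulness of the check. Strengths and limitations presents blinding as a feature of the design. The combined endpoint proposed for the definitive trial includes self-reported falls, and hospitalization reported by patients and practices. The process-evaluation findings are to be used in planning that trial.

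**Working it through.** The article gives no blinding result, power or significance level to reproduce, so the check applies the stated model to the stated size.

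**Inputs.** There are 20 practices, 10 per region. Blocks of 6 and 4 fill 10 places per region, giving 3 + 2 = 5 practices per arm and region and 10 per arm overall. This assumes balanced blocks and full recruitment. One GP guess per practice is also an assumption, because the number of GPs per practice is not stated. The correct-guess rates below are assumed.

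**The model with an empty cell.** Take 10/10 correct in the intervention arm and 5/10 in control.
- Maximum likelihood: log odds ratio = ln(10/0) − ln(5/5), which is infinite. Iteration stopped at 22.6 with a standard error of about 15,241.
- Wald: z = 22.6/15,241 = 0.0015, p = 0.999. As iteration continues, the coefficient grows steadily but the standard error grows exponentially, so z goes to 0 whatever the other arm shows.
- Likelihood ratio: the null −2 log-likelihood at 15/20 correct is −2(15 ln 0.75 + 5 ln 0.25) = 22.49. The fitted value is −2(10 ln 0.5) = 13.86. The difference is 8.63 on 1 df, p = 0.0033.
- Fisher's exact test: p = 0.033.
- Firth-penalised log odds ratio (here equivalent to adding 0.5 to each cell): ln[(10.5/0.5)/(5.5/5.5)] = ln 21 = 3.04, which is finite.

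**Other tables.** With 10/10 in one arm and 0 to 9 of 10 in the other, Wald p stays between 0.9987 and 0.9989, while likelihood-ratio p runs from 1.4 × 10⁻⁷ to 0.23 and Fisher p from 1.1 × 10⁻⁵ to 1. Splits of 8:12, 8:10 and 9:9 behave alike, with Wald p at least 0.998. One wrong guess removes the problem: 9/10 against 5/10 gives log odds ratio ln 9 = 2.20, standard error √(1/9 + 1/1 + 1/5 + 1/5) = 1.23 and Wald p = 0.074 (likelihood ratio 0.044).

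**How often.** P(all 10 intervention GPs correct) = π¹⁰ for a true correct-guess rate π:

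| π | π¹⁰ |
|---|---|
| 0.70 | 3% |
| 0.80 | 11% |
| 0.90 | 35% |
| 0.95 | 60% |
| 0.99 | 90% |

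A control arm guessing at 50% adds almost nothing: all or none correct has probability 2 × 0.5¹⁰ = 0.2%. The chance passes one half only when π exceeds 0.5^(1/10) = 0.93.

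**Per-arm summary.** For 10/10 correct, the exact 95% lower limit is 0.025^(1/10) = 0.69, so the interval is 69% to 100%. The exact two-sided test against 50% gives p = 2 × 0.5¹⁰ = 0.002. If both arms are 10/10 correct, every between-arm contrast gives p = 1 (Firth log odds ratio 0, Fisher p = 1). Only the per-arm proportions then show that blinding failed.

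**The case against.** The strongest case on the other side is that the article says only logistic regression. It names neither the Wald test nor unpenalised estimation, and a condensed article commonly leaves such detail to an analysis plan, which is not at hand here. The p-value near 1 belongs to the Wald test; the likelihood-ratio test of the same model gives p = 0.003 on the same data. The data are to be analysed descriptively, a standard error near 15,000 would be noticed, and the interviews in both arms give further evidence on participants' experience. All of this stands, and it limits the weight of the point.

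A reader might infer that the plan would report complete unblinding of the intervention practices as no effect of study arm. The article does not support that, because it has no rule turning a non-significant coefficient into a statement that blinding held. A reader might also infer that separation is the likely outcome. That rests on assumed rates: at 70% to 80% correct the chance is 3% to 11%. The shared guideline material and flyer, and the stepwise release of information to practices, are meant to hold the rate down.

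What remains does not depend on the choice of test. The article names a model and a sample size for which the odds ratio can fail to exist in the situation that the analysis is meant to detect, and it names no remedy.

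**Conclusion.** The point holds as a limitation of the stated method. With about 10 GPs per arm, complete correct guessing in one arm leaves the odds ratio without a finite estimate and makes a default Wald p-value meaningless (0.999, against 0.003 by likelihood ratio and 0.033 by Fisher for 10/10 against 5/10). The chance of this runs from about 3% to 90% over assumed intervention-arm rates of 70% to 99%, and the documents do not show where in that range the trial will fall. The calculation assumes one guess per practice, full recruitment and balanced blocks; moderate imbalance does not change the picture. Severity is minor, because this is a secondary exploratory analysis in a pilot with no confirmatory test.

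**What to change.** In the Analysis section, make the 2x2 table of guess by arm the main GP-level blinding result. Report the proportion correct in each arm with an exact 95% confidence interval, compared with 50%. This also covers the case in which both arms guess correctly throughout, which no between-arm contrast can show. For any contrast between arms, use an exact test or Firth-penalised logistic regression, and state that Wald results are not reported when a cell is empty. State how many GP guesses each practice contributes.

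The cost is one or two sentences and no new data. The downside is that exact intervals are wide at 10 per arm: even 10/10 correct leaves a lower limit of 69%.
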